## Abstract

**Background:**

Spinal cord stimulation (SCS) has been shown to provide pain relief for chronic back and leg pain due to failed back surgery syndrome. But many patients with chronic back pain have not had major back surgery or are not good candidates for surgery, and conventional medical management (CMM) provides limited relief. We have termed this condition nonsurgical refractory back pain (NSRBP). Level 1 evidence does not yet exist showing the therapeutic benefit of SCS for NSRBP.

**Objective:**

To compare 10‐kHz SCS plus CMM (10‐kHz SCS + CMM) to CMM alone for treatment of NSRBP in terms of clinical and cost effectiveness.

**Study Design:**

Multicenter, randomized controlled trial (RCT), with subjects randomized 1:1 to either 10‐kHz SCS + CMM or CMM alone. Optional crossover occurs at 6 months if treatment does not achieve ≥50% pain relief.

**Methods:**

Patients with NSRBP as defined above may be enrolled if they are ineligible for surgery based on surgical consultation. Subjects randomized to 10‐kHz SCS + CMM will receive a permanent implant if sufficient pain relief is achieved in a temporary trial. Both groups will receive CMM per standard of care and will undergo assessments at baseline and at follow‐ups to 12 months. Self‐report outcomes include pain, disability, sleep, mental health, satisfaction, healthcare utilization, and quality of life.

**Results:**

Enrollment was initiated on September 10, 2018. Prespecified independent interim analysis at 40% of the enrollment target indicated the sample size was sufficient to show superiority of treatment at the primary endpoint; therefore, enrollment was stopped at 211.

**Conclusions:**

This large multicenter RCT will provide valuable evidence to guide clinical decisions in NSRBP.

## Introduction

Approximately 13.1% of the U.S. population suffers from chronic low back pain (CLBP)^1^ with the accompanying negative effects on mental health, quality of life, and productivity.^2^ CLBP is a major cause of disability and cost to our healthcare system,^1^ accounting for 3.1% to 4.9% of all emergency room visits,^3^ in addition to the significant cost of lost productivity due to CLBP.^4^

The treatments for CLBP are multimodal and range from topical or oral medication, to physical therapy, to injection therapy and spine surgery.^5^ When CLBP has a clear etiology with a surgical target, then spine surgery is potentially beneficial. If a surgical target is not clear, then the CLBP can be termed nonspecific.^6^ The goal of treatment when the underlying cause of the back pain is not identified or not amenable to treatment is to reduce the symptoms and improve quality of life. In these nonspecific cases, there may be a tendency to overuse opioids or pursue inappropriate surgery.^7^, ^8^

Spinal cord stimulation (SCS) has been utilized for treating chronic pain for multiple decades.^9^ Though efficacy with predominant back pain was typically lower when compared with leg pain,^10^, ^11^, ^12^ newer generation SCS therapies have shown improved results with predominant back pain.^13^, ^14^, ^15^ SCS is considered an effective treatment for failed back surgery syndrome (FBSS) and complex regional pain syndrome of the lower extremities.^13^, ^16^, ^17^, ^18^, ^19^ It is also considered a safe and reversible therapy, with serious complications rarely observed.^20^ Kumar et al.^21^ presented a randomized controlled trial (RCT) with a design similar to that of the present study but in an FBSS population, showing that SCS was superior to CMM in a number of clinical outcomes. The published RCTs studying the efficacy of SCS for CLBP have included mostly patients with FBSS but also some surgery‐naïve patients. The efficacy of SCS for surgery‐naïve patients appears promising based on small prospective series^22^, ^23^, ^24^ and subanalysis of larger studies.^13^, ^25^, ^26^

A small feasibility study targeting surgery‐naïve patients with chronic refractory back pain who were not candidates for surgery demonstrated significant clinical efficacy out to 36 months in terms of pain, disability, and opioid reduction with high‐frequency SCS at 10 kHz (10‐kHz SCS).^27^ We use here the terminology *nonsurgical refractory back pain* (NSRBP) to represent this patient group (Figure 1). Higher level evidence is needed to demonstrate the clinical efficacy and cost effectiveness of 10‐kHz SCS in this population, which otherwise has limited therapeutic options.^28^

**Figure 1 papr12945-fig-0001:**
[figure not shown]
Schematic showing the criteria for non‐surgical refractory back pain population.

### Study Goals and Objectives

The primary objective of this clinical trial is to evaluate the clinical effectiveness of the addition of 10‐kHz SCS therapy to current conventional medical management (CMM) for NSRBP. Clinical efficacy will be measured in terms of patient‐reported pain relief, disability, quality of life, and change in opioid use. Secondly, the investigation will generate data on the cost effectiveness of the addition of 10‐kHz SCS therapy to CMM in terms of healthcare utilization (HCU) and productivity.

## Methods

The study is a randomized, controlled, multicenter trial investigating the clinical and cost effectiveness of 10‐kHz SCS for NSRBP when used in addition to CMM.^29^ Up to of 216 patients with NSRBP will be randomized 1:1 to receive either CMM alone or 10‐kHz SCS in addition to CMM (10‐kHz SCS + CMM). The total follow‐up period is 12 months for all participants, with an optional crossover at 6 months. Subjects may be withdrawn from the study for reasons such as entry criteria failure, trial failure, subject or investigator request, lost to follow‐up, subject pregnancy, or adverse event. The study protocol and reporting followed Consolidated Standards of Reporting Trials (CONSORT) guidelines, and the outcomes included were based on the guidelines from the Initiative on Methods, Measurement, and Pain Assessment in Clinical Trials (IMMPACT).^30^ The trial registration number is NCT03680846.

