### 10‐kHz SCS + CMM Group

Subjects randomized to 10‐kHz SCS + CMM will undergo a 14‐day SCS trial phase. Two percutaneous leads with 8 contacts each will be placed in the epidural space spanning vertebral levels T8 to T11.^13^ Stimulation at a frequency of 10 kHz and pulse width of 30 µicroseconds will be delivered from an external pulse generator. The stimulation target and current amplitude will be adjusted until at least 50% self‐reported back pain reduction from baseline is achieved, defined as trial success, or until conclusion of the trial phase. Subjects who pass the trial phase will be scheduled for permanent implantation of the 10‐kHz SCS system (Senza, Nevro Corp., Redwood City, CA, U.S.A.) with investigator and subject agreement. Subjects who fail the trial phase will have leads explanted and will not receive a permanent SCS system but will be followed‐up for 6 months.

The permanent device implantation procedure will be per the manufacturer’s physician implant manual and standard of care. The leads will be placed trans‐fascially and anchored to the fascia, and will be tunneled to a subcutaneous pocket where the implantable pulse generator (IPG) is housed. The IPG is typically implanted in the lower back/buttock region. The device will be activated 0 to 14 days following permanent implantation. The subject will be instructed on the use of the IPG charger and remote control. Programming adjustments will be made at scheduled follow‐ups as needed.

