### Data Management and Statistical Analysis

Descriptive statistics will be used to summarize all subject baseline and outcome data collected during the study. Continuous variables will be summarized using means, standard deviations, and ranges. Categorical variables will be summarized in frequency distributions.

Analysis populations defined for the study include intention‐to‐treat (ITT) and per protocol (PP). The ITT population includes all randomized subjects, while the PP population includes subjects who completed the visit corresponding to the endpoint being analyzed. Note that subjects who fail the temporary trial will be included in the ITT population for the high‐frequency stimulation at 10 kHz (HF10) + CMM arm.

The primary endpoint will be evaluated with a Fisher’s exact test comparing the percentage of subjects in each group who achieve a 50% improvement in their back pain VAS score at the primary efficacy assessment in the ITT population. The following secondary endpoints will be successively evaluated (hierarchical closed test approach) at study completion in the order shown with a 0.05 significance level for difference between groups in the PP population until statistical significance is not achieved.

The comparison between HF10 + CMM and CMM alone in terms of healthcare resource use (HRU) will be made based on doctor’s office visits, emergency room visits, or hospital stays, as well as on medical tests and procedures. Medication use (opioids and medication for CLBP), work status, health status (12‐Item Short Form Survey [SF‐12]), quality of life (EuroQol 5‐Dimension, 5‐Level Instrument [EQ‐5D‐5L]) will be used in the cost‐effectiveness analysis. The change from baseline to 6‐month follow‐up will be compared for CMM vs. HF10 + CMM for all these parameters. In addition, subjects can be used as their own control comparing HRU at baseline to HRU after baseline for the HF10 + CMM arm, or pre‐ and post‐crossover for those crossing over from the CMM to HF10 + CMM at 6 months. Parametric functions (eg, Weibull, Gompertz, etc.) will be used to extrapolate from 6‐month HRU to 1, 2, and 3 years out. HRU will be associated with direct medical costs using fee schedules, Medicare claims, and peer‐reviewed literature. Changes in EQ‐5D‐5L index scores will be used to assess changes in health status and the economic value of the addition of HF10 to CMM.

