### Missing Data

Since the primary analysis of the primary study endpoint at 3 months will be in the ITT population, a sensitivity analysis will be performed to examine the impact of any missing data on the observed results. This sensitivity analysis will use the multiple imputation method for estimating missing primary endpoint data, based on available baseline, 1‐month, and 3‐month follow‐up data.

All other analyses of secondary, tertiary, and exploratory analyses will be based on the PP population and available data. In the case of questionnaires with established rules for scoring results in the presence of isolated missing items, those rules will be followed.

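### The protocol gives conflicting follow-up rules for SCS trial failures, and withdrawing them would leave one-sided, outcome-dependent gaps in the 3-month primary endpoint

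*Protocol article*

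**What the plan says.** Four parts of the protocol article bear on a subject who is randomized to 10-kHz SCS + CMM and fails the temporary trial.

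- **Methods, opening paragraph.** Trial failure is a listed reason for leaving: "Subjects may be withdrawn from the study for reasons such as entry criteria failure, trial failure, subject or investigator request". The same paragraph says "The total follow‐up period is 12 months for all participants".
- **10-kHz SCS + CMM Group.** The trial phase lasts 14 days, and success is at least 50% self-reported back pain reduction from baseline. Those who fail "will not receive a permanent SCS system but will be followed‐up for 6 months".
- **Data Management and Statistical Analysis.** In the SCS arm, "subjects who fail the temporary trial will be included in the ITT population". The test is fixed: "The primary endpoint will be evaluated with a Fisher’s exact test", in the ITT population. The article states no rule for missing values in that test.
- **Missing Data.** "This sensitivity analysis will use the multiple imputation method for estimating missing primary endpoint data". The inputs named are the available baseline, 1-month and 3-month data. Trial outcome and implant status are not mentioned.

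**The concern.** The same subjects may be withdrawn, are to be followed for 6 months, and belong to a study that follows everyone for 12. Which rule a site applies decides whether a trial failure has a 3-month VAS.

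This matters more than ordinary attrition for three reasons. Before the crossover at 6 months only the SCS arm has a trial phase, so this exit is open in one arm only. The exit depends on outcome, because trial success and 3-month response use the same 50% back pain threshold. And the trial is unblinded (Limitations), so a discretionary withdrawal is made with the allocation known.

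If failures leave without a 3-month VAS, the observed part of the SCS arm consists almost wholly of implanted subjects. An analysis that uses only that part, or imputes from it without knowing who failed, moves the SCS responder rate upwards.

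**Working it through.** **1. The plan's own figure.** The Sample Size Calculation section assumes 60% versus 36% responders, two-sided alpha 0.05, Fisher's exact test and 98 per group. Exact enumeration gives power 0.907, so the stated 90% is reproduced. The design difference is 60 − 36 = 24 points.

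**2. Which rule produces missing data.**

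| Rule applied to a trial failure | 3-month VAS |
|---|---|
| Followed for 6 months | Observed; nothing to impute |
| Followed for 12 months | Observed; nothing to impute |
| Withdrawn at trial failure | Missing; the 1-month value may be missing too, as the trial lasts 14 days |

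The 6- versus 12-month discrepancy does not by itself touch the 3-month endpoint. The withdrawal clause does.

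**3. Size of the excess if failures are withdrawn.** Let f be the share of the SCS arm that fails and is withdrawn, r the response rate of implanted subjects, and q the true 3-month response rate of failures.

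- True arm rate: (1 − f)r + fq
- Rate returned by dropping failures, or by imputing them at the implanted rate: r
- Excess: r − [(1 − f)r + fq] = f(r − q)

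The documents give none of f, r or q for these subgroups. Assumed ranges: f = 10% and 20%; r = 60% and 70%; q = 0% (failures never respond) and q = 36% (the CMM rate in the sample size section, since all subjects continue CMM).

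| f | r | Excess at q = 0% | Excess at q = 36% |
|---|---|---|---|
| 10% | 60% | 0.10 × 60 = 6.0 points | 0.10 × 24 = 2.4 points |
| 10% | 70% | 0.10 × 70 = 7.0 points | 0.10 × 34 = 3.4 points |
| 20% | 60% | 0.20 × 60 = 12.0 points | 0.20 × 24 = 4.8 points |
| 20% | 70% | 0.20 × 70 = 14.0 points | 0.20 × 34 = 6.8 points |

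**4. How much a 1-month value helps.** An illustrative large-sample simulation of the SCS arm assumed f = 10%, implanted response 60%, failure response 9%, and correlation 0.7 between 1- and 3-month relief. The true arm rate was 54.8%. The imputation model did not contain trial outcome.

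| Data left by failures | Response imputed to failures | Arm rate |
|---|---|---|
| Baseline only | 60% | 59.9% |
| 1-month value observed | 19% | 55.8% |

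Failures therefore receive about the implanted rate only if they leave before the 1-month visit. With a 1-month value the arm is overstated by about 1 point.

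**5. Effect on false positives of a complete-case Fisher test.** Alpha is 0.025 (the level set in the Interim Analysis section), the true rate is 36% in both arms, and there are 98 per arm before failures are dropped.

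| f | Failures respond at 0% (implanted 36/(1 − f)) | Failures respond at 36% |
|---|---|---|
| 0 | 1.7% | 1.7% |
| 10% | 4.2% (88 left, implanted 40%) | 2.1% |
| 20% | 13.7% (78 left, implanted 45%) | 2.0% |

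The inflation comes entirely from failures responding less often than implanted subjects. If they respond equally often, there is none.

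**The case against.** The best defence is to read the sections together. The Methods list is general and permissive (subjects may be withdrawn), whereas the section on the SCS arm speaks specifically of trial failures and says they will be followed for 6 months. The primary endpoint falls at 3 months, inside that window, so the outcome would be observed. This is a fair reading, and under it the problem largely disappears. But it needs the reader to choose between two statements, and sites acting on the Methods text could choose the other. Brevity is no answer either: the article states conflicting rules, it does not omit one.

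A reader might infer that the plan withdraws trial failures as a rule, and that multiple imputation then turns the primary ITT result into an implanted-only estimate. The documents do not support this. Withdrawal is permitted, not prescribed. Multiple imputation is a sensitivity analysis, and nothing says that the primary Fisher test uses it. The analysis plan, which is not shown, may well put trial or implant status into the model.

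A reader might also take the 4.2% and 13.7% false-positive rates as the expected effect. They hold only if trial failures never respond. At the 36% CMM rate the figure is about 2%.

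What remains is the contradiction itself, and the fact that no analysis plan, however good, recovers a 3-month VAS that was not collected.

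**Conclusion.** The contradiction is certain: the withdrawal clause, the 6-month statement and the 12-month statement cannot all govern the same subjects, who must also be in the ITT analysis. The bias is conditional. It needs failures to be withdrawn, to leave before useful follow-up, and to be dropped from the Fisher test or imputed without trial status. Under those conditions, with an assumed implanted rate of 60–70%, the SCS responder rate is overstated by about 2–7 points at f = 10% and 5–14 points at f = 20%, set against a design difference of 24 points. The lower ends assume that failures respond at 36%, the upper ends at 0%. The direction favours the device whenever failures respond less often than implanted subjects. The actual size cannot be fixed, because the documents give no trial-failure rate.

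**What to change.** - Remove trial failure as a reason to end data collection. Whether a subject receives the device and whether the subject stays in the study are separate matters.
- Reconcile the 6- and 12-month statements, in whatever way the sponsor intends, so that the 3-month VAS is collected for every trial failure.
- In the primary ITT analysis, count any trial failure who still lacks a 3-month VAS as a non-responder.
- Include trial or implant status in the sensitivity imputation model.
- Optionally, add a tipping-point analysis that varies the imputed response by arm.

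The cost is a protocol clarification, a few lines in the analysis plan, and possibly a slightly lower SCS responder rate.

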### Inclusion Criteria

The study will recruit patients with moderate to severe refractory back pain who have not had previous major lumbar spine surgery, are not candidates for back surgery as assessed by a spine surgeon, or decline surgery. Refractory pain was defined based on a published guideline^31^ as failing to reach treatment goals, which may be related to inadequate pain reduction or daily functioning, or intolerable adverse effects. The complete inclusion criteria are listed in Table 1. The inclusion criteria are designed to be pragmatic to mirror those of nonsurgical patients currently seen in the clinic for whom SCS is indicated. Patients are eligible for the study whether they have unilateral, bilateral, or no concomitant leg pain.

**Table 1 papr12945-tbl-0001:** Inclusion Criteria

Have been diagnosed with chronic, refractory*, * axial low back pain and are not a candidate for surgery based on a spine surgeon’s assessment Pain should have a predominant neuropathic component as per the investigator’s clinical assessment Have not had any surgery for back or leg pain, or any surgery resulting in back or leg pain Considering daily activity and rest, have average back pain intensity of ≥5 out of 10 cm on the VAS at enrollment Be on no or stable pain medications, as determined by the investigator, for at least 28 days prior to enrolling in this study Be 18 years of age or older at the time of enrollment Be willing and capable of giving informed consent Be willing and able to comply with study‐related requirements, procedures, and visits Be capable of subjective evaluation, able to read and understand written questionnaires in the local language, and able to read, understand, and sign the written inform consent

* Pain is defined as refractory, regardless of etiology, when conventional medical management has failed to reach treatment goals that may include adequate pain reduction and/or improvement in daily functioning or have resulted in intolerable adverse effects.

### Exclusion Criteria

The exclusion criteria are designed to mirror the contraindications for SCS implantation in clinical use or pertain to patients being able to accurately report pain for study assessments (Table 2).

**Table 2 papr12945-tbl-0002:** Exclusion Criteria

Have a diagnosed back condition with inflammatory causes of back pain (eg, ankylosing spondylitis or diseases of the viscera) Have a medical condition or pain in other areas, not intended to be treated with SCS, that could interfere with study procedures or accurate pain reporting, and/or confound evaluation of study endpoints, as determined by the investigator Have evidence of an active disruptive psychological or psychiatric disorder identified as the primary condition or other known condition significant enough to impact perception of pain, compliance of intervention, and/or ability to evaluate treatment outcome, as determined by the investigator in consultation with a psychologist Have a current diagnosis of a progressive neurological disease, spinal cord tumor, or severe/critical spinal stenosis Have a current diagnosis of a coagulation disorder, bleeding diathesis, progressive peripheral vascular disease, or uncontrolled diabetes mellitus that would add unacceptable risk to the procedure Be benefitting within 30 days prior to enrollment from an interventional procedure to treat back and/or leg pain*, * Have an opioid addiction or drug‐seeking behavior as determined by the investigator Have an existing drug pump and/or SCS system or another active implantable device such as a pacemaker Have prior experience with neuromodulation devices (SCS, PNS, DRG stimulation, multifidus muscle stimulation) Have a condition currently requiring or likely to require the use of diathermy or MRI that is inconsistent with Senza system guidelines in the physician’s manual Have metastatic malignant disease or active local malignant disease Have a life expectancy of less than 1 year Have an active systemic or local infection Be pregnant (participants of child‐bearing potential that are sexually active must use a reliable form of birth control) Have within 6 months of enrollment a significant untreated addiction to dependency‐producing medications or have been a substance abuser (including alcohol and illicit drugs) Be concomitantly participating in another clinical study Be involved in an injury claim under current litigation Have a pending or approved worker’s compensation claim

CMM, conventional medical management; DRG, dorsal root ganglion; PNS, peripheral nerve stimulation; SCS, spinal cord stimulation.

* Interventions should not be performed less than 30 days prior to enrollment or a follow‐up visit to ensure that the pain level is stable and representative of their long‐term response to CMM.

### Participants

Patients will be recruited in 15 centers in the United States. In all centers, patients who have not obtained satisfactory results with CMM and have not had previous major lumbar surgery will be screened for eligibility by medical record review. Consent will be obtained from potential candidates and the following screening assessments will be performed: back and leg pain on the VAS, magnetic resonance imaging (MRI), x‐rays with or without flexion‐extension views if indicated, and surgical consultation. Inclusion requires a diagnosis of chronic axial low back pain with a neuropathic component. Candidates will complete the PainDETECT questionnaire for assessment of a neuropathic pain component.^32^ The PainDETECT questionnaire will be used to guide the investigators’ assessments, but the score will not be used to automatically exclude potential subjects since the literature is mixed in terms of validating its use in the detection of neuropathic back pain.^33^ Appropriate interventional procedures should have been tried prior to enrollment with continued refractory pain.^31^ All patients were required to have an MRI‐based diagnosis and spine surgical expert opinion that surgical intervention was not indicated. If all eligibility criteria are met, demographics and baseline assessments will be collected, and subjects will be randomized.

